## Objectives

The primary objective of the study is to analyze the different efficacies of rTMS in AD patients with different APOE genotypes, so as to provide the basis for the precise treatment of AD.

The secondary objective is to analyze the changes in gamma oscillations and pathological indicators in different APOE genotypes, thus being conducive to the precise treatment of AD.

## Methods

### The Recruitment and Inclusion of Alzheimer’s Disease Patients

The patients are recruited in two main ways: (1) Online recruitment: our recruitment program was announced on our hospital’s official website in February this year^1^. Then, all eligible Alzheimer’s disease patients could apply for rTMS treatment by filling in the online form.

(2) Hospital system: The hospital information retrieval system are also adopted to obtain information about patients with cognitive impairment and call to ask if they would like to participate in the recruitment program. Then, those who are interested in the program will enter into our patient recruitment diagnostic process.

These candidates applying for rTMS treatment will undergo neuropsychological assessments in the outpatient clinic of our hospital. Then, those with cognitive impairment are recommended for MRI scanning so as to assess the extent of hippocampal atrophy, while those with an MTA score ≥ 2 are the potential AD patients, which are diagnosed by the neuroimaging specialist (Figure 1). In addition to that, the data of these patients will be further evaluated by two neurologists. Furthermore, the eligible applicants for a clinical diagnosis of Alzheimer’s disease should meet our inclusion criteria and exclusion criteria. Beyond that, they should sign a subject informed consent form with our research team. Here, it should be mentioned that before rTMS treatment, patient blood samples were collected for APOE genotyping (Table 1).

**FIGURE 1 F1:**
[figure not shown]
Flow chart of the present RCT study. MMSE, Mini Mental State Examination; rTMS, repetitive transcranial magnetic stimulation; MoCA, Montreal Cognitive Assessment Scale; ADAScog, Assessment Scale-cognitive subscale; Center for Epidemiologic Studies Depression Scale (CES-D); Activity of Daily Living (ADL); MSD, Meso Scale Discovery.

**TABLE 1 T1:** APOE genotyping is determined by promoter polymorphisms of two single nucleotides (rs429358 and rs rs7412).

APOE genotypes	S1:rs429358	S2:rs7412
E2/E2	T/T	T/T
E3/E3	T/T	C/C
E4/E4	C/C	C/C
E2/E3	T/T	T/C
E2/E4	T/C	T/C
E3/E4	T/C	C/C

*T or C represents the first DNA base of the nucleotides.*

The inclusion and exclusion criteria are as follows:

**Inclusion criteria**

(1)The age ranges from 50 to 85 years old.(2)Subjective perception of memory loss more than 1 year; MMSE ≤ 26 (level of education more than 7 years: MMSE ≤ 26; level of education 1–7years: MMSE ≤ 24; level of education less than 1 year: MMSE ≤ 19).(3)MRI exhibits medial temporal atrophy (hippocampus, entorhinal cortex, amygdala); MTA visual evaluation scale ≥ 2.

**Exclusion criteria**

(1)There was a history of severe brain lesions or brain surgery, such as brain tumor, hydrocephalus and intracranial hematoma.(2)The patients have received TMS treatment, transcortical electrical stimulation, deep brain electrical stimulation, or vagus nerve electrical stimulation prior to application.(3)There are serious complications, such as frequent seizures, brain tumor surgery, intracranial infection, serious heart disease, lung disease, mania, and severe mental disorders.(4)The patient had an implanted pacemaker, defibrillator, cochlear implant, other nerve stimulator, or steel plate, and could not accept TMS therapy or MRI scanning.(5)The patient suffers frontotemporal dementia, vascular dementia, Lewy body dementia, or other diseases.(6)White matter lesions with a Fazekas score > 3 and cerebral infarction in medial temporal lobes were excluded.(7)Others referred to the NINCDS-ADRDA exclusion criteria (revised—2007) (Dubois et al., 2007).

**Exit criteria**

(1)Subjects voluntarily withdraw from the study for personal reasons.(2)Subjects are unable to continue to participate in the study due to a serious medical condition, such as a cardiovascular accident, or those that would have a significant impact on the study results.(3)Subjects developed serious treatment-related complications, are unable to tolerate the treatment dose or could not complete the associated assay.

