### Randomization and Allocation

#### Stratified Randomized Groups

In this study, 48 APOE4 carrier AD patients (APOE4-AD) and 32 non-APOE4 carrier AD patients (Non-APOE4-AD) will be recruited. Then, they will be assigned to the HF-rTMS group and the LF-rTMS group based on the stratified randomization method: 40 for the HF-rTMS group and 40 for the LF-rTMS group, while in subgroups, 24 patients will be assigned to in the APOE4-HF group, 24 patients will be assigned to the APOE4-LF group, 16 patients will be assigned to non-APOE4-HF group, and 16 will be assigned to the non-APOE4-LF group. The specific process is as follows: Our team members consist of quality control personnel, TMS therapy physicians, neuropsychological assessors and laboratory staff. Specifically, quality control personnel are responsible for quality control of study data and grouping randomization; TMS therapy physicians perform TMS treatment based on information from quality control personnel; neuropsychological assessors conduct neuropsychological assessments before, during and after treatment and follow-up; laboratory staff are in charge of blood sample processing and testing. In addition, the grouping randomization information will not be released by quality control personnel until the primary endpoint of the study has been met for all program participants at follow-up (Table 1).

The postadmission randomization process are performed by the quality control staff. Specifically, the admission sequence of APOE4 carriers and non-carriers was 1–48 and 1–32, respectively, and the admission numbers of carriers and non-carriers were randomized using Excel sheet randomization to assign them within the HF-rTMS and LF-rTMS groups, respectively. When the follow-up of all subjects reached the clinical trial endpoint, the project quality control staff and the project leader verified the grouping information for unblinding and summarized the project data for statistical analysis.

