### Sample Size Calculation

The sample size of this project was calculated by Pass software on the basis of previous literature. In this study, the MMSE scores of the HF-rTMS group and the LF-rTMS group were 10.4 ± 1.7 and 10.2 ± 1.8, respectively, before treatment. After 2 weeks of rTMS treatment, their MMSE scores reached 11.2 ± 1.9 and 8.8 ± 2.3, respectively (Ahmed et al., 2012), when the target effect size had 80% power (β = 0.10) and a type I error was 5% (α = 0.05). In addition, the group sample size of 13 and 12 achieved 81% power for detecting a difference of 2.4 between the null hypothesis and that the mean of both groups is 11.2 and the alternative hypothesis that the mean of Group 2 is 8.8 with known group standard deviations of 1.9 and 2.3 and a significance level (alpha) of 0.050 using a two-sided two-sample *t*-test, while the sample size of each subgroup is at least 13. Considering the loss of follow-up, falling off and sample data being eliminated due to data quality, the sample size should be increased by 20%. Thus, the final sample size of each subgroup are at least 16. Furthermore, the ratio of APOE4 carriers to non-APOE4 carriers are set to 3:2 according to the comparison of population samples and our previous study. Other than that, in this study, 80 participants, with 48 APOE4 carriers and 32 non-APOE4 carriers will be recruited.

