### Quality Control and Quality Assurance

Two neuroscientists, a neuroimaging specialist and an expert in geriatrics, worked together to examine the participants and provide a diagnosis for each participant. In addition, training was provided for all researchers, while all items involved in the test, such as blood samples, EEG data processing and neuropsychological assessments were monitored by the quality control committee who randomly selected data samples to send to a third party for retesting or re-evaluation. Data entry was performed by EpiData Entry software and was also monitored by the quality control committee who further randomly selected the input information and paper information. To control the impacts of clinical treatment, we strictly restricted medication. Oral medication before and during hospitalization as well as during follow-up remained unchanged except for sudden diseases, such as cardiovascular and cerebrovascular accidents and aggravation of primary diseases. If there are errors, the sampling proportion will be expanded, while if the input error proportion is high, a second person needs to check and correct the input data. Moreover, all data were monitored and reviewed by the principal investigator or research coordinators.

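### Study exit for reasons that arise after randomisation, and data quality control by those who hold the allocation, put the randomised HF–LF comparison at risk of bias

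*Protocol article*

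**What the plan says.** Four parts of the protocol article bear on this.

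- **Exit criteria.** Besides voluntary withdrawal, a patient leaves for a serious medical condition "or those that would have a significant impact on the study results". A patient also leaves after serious treatment-related complications, or if they "are unable to tolerate the treatment dose or could not complete the associated assay". The criteria concern leaving the study; nothing separates that from stopping stimulation.
- **Sample Size Calculation.** Thirteen per subgroup is raised by 20% to 16. The reasons given are loss to follow-up, dropout and "sample data being eliminated due to data quality".
- **Stratified Randomized Groups.** One role has two tasks: "quality control personnel are responsible for quality control of study data and grouping randomization". The same personnel keep the allocation: "the grouping randomization information will not be released by quality control personnel until the primary endpoint of the study has been met". At the end, the quality control staff and the project leader "verified the grouping information for unblinding and summarized the project data for statistical analysis".
- **Quality Control and Quality Assurance.** Blood samples, EEG processing and neuropsychological assessments are "monitored by the quality control committee who randomly selected data samples to send to a third party for retesting or re-evaluation". Data entry is also checked against paper records.

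The primary outcome is MMSE (Outcomes), read at the end of treatment and at the 3-month follow-up (Statistical Hypothesis).

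**The concern.** Randomisation protects the HF–LF comparison only while the patients compared are those who were randomised. Intolerance and treatment complications can occur only after allocation, and the arms differ in stimulation frequency, so exit rates could differ by arm. An uncompleted EEG or blood assay can also end participation, although the primary outcome is a cognitive score that needs neither. The impact-on-results ground has no threshold and names nobody to decide it.

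If patients who leave have different MMSE courses from those who stay, and leave at different rates in the two arms, the difference in means among those remaining mixes the treatment effect with selection. A second route to bias opens if exits or data eliminations are settled by people who know the arm. The article puts data quality control and the allocation in the same hands and states no blinding for these decisions. A superiority claim tested in subgroups as small as 16 v 16 has little room for either.

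**Working it through.** **1. The plan's own figure.** Inputs from Sample Size Calculation: difference 2.4, SDs 1.9 and 2.3, groups of 13 and 12, two-sided alpha 0.05.

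- Standard error = sqrt(1.9²/13 + 2.3²/12) = sqrt(0.2777 + 0.4408) = 0.848.
- Power with known SDs = Φ(2.4/0.848 − 1.96) = Φ(0.87) = 80.8%, which reproduces the stated 81%.
- Inflation: 13 × 1.2 = 15.6, rounded up to 16, as stated.

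The inflation makes sense only if the plan expects exits and eliminated data to reduce the number analysed. The allowance is 16 − 13 = 3 of 16 per subgroup (18.75%), and it also covers ordinary dropout.

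**2. Size of a possible bias.** Let a fraction f of an arm be lost, and let those patients average D MMSE points worse than those kept. The full-arm mean is (1 − f) × kept + f × lost, so the kept mean exceeds it by f × D. The bias in the HF–LF difference is (f₁ − f₂) × D. The article gives neither f by arm nor D; both are assumed.

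| Lost, arm 1 v arm 2 | D = 1 | D = 3 | Share of 2.4 |
|---|---|---|---|
| 20% v 5% | 0.15 | 0.45 | 6% to 19% |
| 20% v 0% | 0.20 | 0.60 | 8% to 25% |

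Both rows treat about the whole allowance as selective loss in one arm, so they lie towards the unfavourable end. With equal loss and equal D in both arms the bias is zero.

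**3. Upper illustration for the type I error.** This is a simulation with no true difference, SD = sqrt((1.9² + 2.3²)/2) = 2.11, the lowest outcomes removed from one arm only, a two-sided t-test at 0.05 and 20,000 runs.

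| Per arm | Removed from one arm | False difference (points) | Type I error |
|---|---|---|---|
| 40 | 2 / 4 / 8 | 0.21 / 0.40 / 0.72 | 8% / 15% / 36% |
| 16 | 1 / 2 / 3 | 0.24 / 0.46 / 0.66 | 7% / 11% / 15% |

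This is a worst case by construction. It shows how few selective losses are needed, not what is expected.

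**The case against.** The strongest reply is that a list of exit reasons is not an analysis rule. The article does not say that MMSE scores already collected from exited patients are discarded. The analysis population may be defined in the full protocol or an analysis plan, neither of which is shown. That stands: the lack of an analysis-set statement is not counted as a fault here, and a reader who infers that HF–LF is no longer a comparison of the randomised groups goes further than the text allows.

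Two other strong readings also fail.

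- **Removal of patients because of their own results.** The word "those" in the second exit criterion most naturally refers to medical conditions, such as an intercurrent event that confounds cognition. Removal by outcome is not stated.
- **Allocation holders choosing which data to drop.** No section says who decides eliminations. The quality control described is random retesting, wider sampling after errors, and second-person checking, which corrects data rather than deletes them. The committee that does it may not be the same people as the personnel who hold the allocation.

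It is also fair that the bias figures are assumptions multiplied together, and that the 20% covers ordinary dropout too.

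The following remains. Exit is from the study and partly for reasons caused by treatment. A missed assay can end participation in a trial with an MMSE endpoint. Even read as medical conditions, the impact-on-results ground makes expected effect on the data a test for leaving. The sample size counts on these losses reducing the analysed number. One role holds both the allocation and responsibility for data quality, with no stated blinding of the decisions.

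**Conclusion.** The point holds as a risk. The exit and elimination provisions are open-ended, depend partly on events after allocation, and are not stated to be applied blind to arm, while those who hold the allocation also have the data quality role. The documents do not establish that the comparison is already compromised, that patients are removed for their outcomes, or that unblinded staff delete data.

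The size depends on unknown loss by arm. Under the assumed 20% v 5% or 20% v 0% and D from 1 to 3 points, the bias is 0.15 to 0.60 MMSE points, or 6% to 25% of the 2.4-point target. It is nil if losses are balanced and similar in kind. The documents give no tolerability data by arm, so neither the direction nor the likelihood can be settled from them. The change should be made before unblinding; at the time of the article 18 of 80 patients had been included.

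**What to change.** Leave the clinical rules for stopping stimulation as they are, and make these changes around them.

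1. Separate stopping treatment from leaving the study. Patients who stop stimulation or miss an EEG or blood assay keep the scheduled MMSE visits unless they withdraw consent or cannot attend.
2. State that the primary analysis includes all randomised patients in the arm assigned.
3. Clarify the second exit criterion, and state that expected impact on the study results is not a ground for removing a patient or data from the analysis.
4. Have exits on non-clinical grounds and all data eliminations decided and documented before unblinding by existing team members blind to arm, for example the project leader, and not by those who hold the allocation list.
5. Do not hand the full list to the treating physicians. Admission numbers run 1–48 and 1–32, so the list would show them upcoming assignments and weaken concealment.

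The cost is protocol wording, a reassigned decision, some off-treatment attendance at visits already scheduled, and slight dilution of the effect estimate. In partial return, on the plan's own inputs and before any dilution, known-SD power is 89.6% with all 16 per group analysed, against 82.7% with 13 per group.

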### Apolipoprotein E Genotyping

DNA was extracted from the patients’ peripheral blood. Then, genotyping was performed by snapshot SNP typing. In addition, APOE alleles and genotypes were determined by sequencing rs429358 and rs7412 at exon 4 of the APOE gene. Furthermore, APOE status was defined by the possessing one or more copies of E2, E3 and E4, whereas APOE ε4 positive status was confirmed as the ε4/ε4; ε3/ε4 or ε2/ε4 (Risacher et al., 2015). In the experimental steps, 2 ml anticoagulant peripheral venous blood was taken to extract leukocytes, genomic DNA was extracted from blood samples by silicon matrix adsorption column method for PCR amplification of target genes, and then the PCR products were purified. After snapshot extension reaction, sequencing and analysis were carried out. The primer sequences used for genotyping were:rs429358-F: AATC GGAACTGGAGGAACAAC; rs429358-R: GATGGCGCTGAG GCCGCGCTC; rs7412-F: AATCGGAACTGGAGGAACAAC; rs7412-R: GATGGCGCTGAGGCCGCGCTC.

### Randomization and Allocation

#### Stratified Randomized Groups

In this study, 48 APOE4 carrier AD patients (APOE4-AD) and 32 non-APOE4 carrier AD patients (Non-APOE4-AD) will be recruited. Then, they will be assigned to the HF-rTMS group and the LF-rTMS group based on the stratified randomization method: 40 for the HF-rTMS group and 40 for the LF-rTMS group, while in subgroups, 24 patients will be assigned to in the APOE4-HF group, 24 patients will be assigned to the APOE4-LF group, 16 patients will be assigned to non-APOE4-HF group, and 16 will be assigned to the non-APOE4-LF group. The specific process is as follows: Our team members consist of quality control personnel, TMS therapy physicians, neuropsychological assessors and laboratory staff. Specifically, quality control personnel are responsible for quality control of study data and grouping randomization; TMS therapy physicians perform TMS treatment based on information from quality control personnel; neuropsychological assessors conduct neuropsychological assessments before, during and after treatment and follow-up; laboratory staff are in charge of blood sample processing and testing. In addition, the grouping randomization information will not be released by quality control personnel until the primary endpoint of the study has been met for all program participants at follow-up (Table 1).

The postadmission randomization process are performed by the quality control staff. Specifically, the admission sequence of APOE4 carriers and non-carriers was 1–48 and 1–32, respectively, and the admission numbers of carriers and non-carriers were randomized using Excel sheet randomization to assign them within the HF-rTMS and LF-rTMS groups, respectively. When the follow-up of all subjects reached the clinical trial endpoint, the project quality control staff and the project leader verified the grouping information for unblinding and summarized the project data for statistical analysis.

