## Abstract

To date, there is a shortage of effective treatment strategies for Alzheimer’s disease (AD), and although repetitive transcranial magnetic stimulation (rTMS) can improve AD cognitive function, there are obvious individual differences, which may be related to different apolipoprotein E (APOE) genotypes. As the risk and pathogenesis of AD varies greatly among different genotypes precise treatment strategies should be implemented depending upon genotype, which has not been proved by clinical studies. Apart from that, the published clinical studies are highly heterogeneous, and therefore, systematic and well-developed randomized controlled Trails (RCT) and demonstration of precise administration protocols are required. To verify this hypothesis, this project designed a RCT study, and randomly divided apoE4 carrier AD and non-carrier AD into high-frequency rTMS (HF-rTMS) or low-frequency rTMS (LF-rTMS) treatment groups. Specifically, 80 patients with AD, namely 48 APOE4 carriers and 32 non-APOE4 carriers will be included in the study. After that, based on different stimulation frequencies of rTMS, they will be divided into the HF-rTMS group and the LF-rTMS group, when patients with AD will be randomly assigned to different treatment groups. After AD patients are involved in the study, their memory, cognition, anxiety, depression and activities of daily living will be tested before and during 2 weeks of rTMS. Furthermore, peripheral blood will be collected before and after treatment to detect changes in pathological indexes via MSD platform (Meso Scale Discovery), while 32-channel EEG data will be also collected to detect and analyze changes in gamma oscillation. In addition, these patients will be followed up for 6 months and their neuropsychological scale was also evaluated every month. At present, our study has included 18 AD patients (10 APOE4 carriers; 8 non-carriers). Our study is still in progress. The grouping has not been unblinded. But the preliminary data demonstrated that non-carriers had better MoCA score improvement than APOE4 carriers. The results indicated that the two populations of AD patients should be treated differently. Thus, this project will provide direction for precision rTMS in AD and also promotes a shift in relevant treatment philosophy.

**Clinical Trial Registration:** [www.ClinicalTrials.gov], identifier [ChiCTR2100041625].

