### Study Process

After AD patients are included in the study, their neuropsychological scales, including cognition, anxiety, depression, activities of daily living and other scales will be assessed. Then, they will be assigned to HF-rTMS or LF-rTMS group and accept due treatment for 2 weeks. During the treatment, the neuropsychological scales will be assessed every week. In addition, blood test results and 32-channel EEG data will be collected before and after treatment, while a 6-month follow-up will be carried out after treatment (Figure 1).

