#### Statistical Hypothesis

The primary endpoint of this study was the end of treatment and completion of the 3-month follow-up for all subjects, and its indicator was the MMSE score. Apart from that, the study hypothesis is to demonstrate the superiority of HF-rTMS over LF-rTMS in transcranial magnetic stimulation protocols for patients with Alzheimer’s disease. In terms of subgroup analysis, the HF treatment group was preferentially compared with the low-frequency treatment group of non-APOE4 carriers; if the statistical result of *P*-value is less than 0.05, then the comparison between the HF treatment group and the low-frequency treatment group of APOE4 carriers is made in order. If the statistical result of *P*-value is less than 0.0125, then the comparison among the four subgroups is considered significant.

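### The plan permits allocation to be released at month 3 while monthly ratings run to month 6, and the staff who hold the list also control data quality

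*Protocol article*

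**What the plan says.** **Release of the allocation.** Stratified Randomized Groups (under Randomization and Allocation) says that grouping "information will not be released by quality control personnel until the primary endpoint of the study has been met for all program participants". The date comes from Statistical Hypothesis: "The primary endpoint of this study was the end of treatment and completion of the 3-month follow-up for all subjects", with MMSE as the indicator. The same subsection on randomized groups ends with a second rule, for breaking the blind: "When the follow-up of all subjects reached the clinical trial endpoint, the project quality control staff and the project leader verified the grouping information for" that step, after which the data are summarized for analysis. That second endpoint is not dated or defined.

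**Length of follow-up.** The Abstract says "these patients will be followed up for 6 months and their neuropsychological scale was also evaluated every month". Study Process agrees: "a 6-month follow-up will be carried out after treatment".

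**Roles.** Stratified Randomized Groups says "quality control personnel are responsible for quality control of study data and grouping randomization". These staff make the Excel allocation and inform the treating physicians. Neuropsychological assessors are listed as a separate role.

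**Data quality.** Sample Size Calculation adds 20%, and one of its reasons is "sample data being eliminated due to data quality". Quality Control and Quality Assurance describes a committee that draws random samples for outside retesting, widens the sampling when errors appear and has a second person correct entries. The principal investigator or coordinators also review all data. None of these people is said to be masked to arm.

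**The concern.** There are two separate issues.

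1. **Timing.** The only stated protection for the allocation is the release rule. If it lapses when the last patient reaches month 3, patients enrolled shortly before that one still have rated visits to come. The scales depend on an interview or on the patient's report, so a rating made with the arm known can shift the HF versus LF comparison at months 4 to 6.

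2. **Dual role.** The people who know each patient's arm are also responsible for the quality of the study data. A decision to query, correct or drop a value can then be taken with the arm in view. Unlike the timing issue, this can reach the primary 3-month MMSE.

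**Working it through.** **Timing: inputs.** Release when the last patient reaches month 3 (Stratified Randomized Groups with Statistical Hypothesis). Monthly visits to month 6 (Abstract). N = 80 (Sample Size Calculation). Accrual length A is not given, so I assume uniform accrual and show A from 6 to 36 months. The 2-week treatment period is the same for everyone and cancels.

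**Formula.** Take a patient enrolled t months before the last one. At release this patient is at month 3 + t, so the month-m visit comes later if t < m − 3. The condition is t < 1 for month 4, t < 2 for month 5 and t < 3 for month 6. Under uniform accrual:

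- share of patients with at least one visit after release = 3/A (A at least 3)
- share of month 4 to 6 visits after release = (1 + 2 + 3)/(3A) = 2/A
- share of all six monthly follow-up visits after release = (1 + 2 + 3)/(6A) = 1/A

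| A (months) | Patients, 3/A | Of 80 | Month 4–6 visits, 2/A | All monthly visits, 1/A |
|---|---|---|---|---|
| 6 | 50% | 40 | 33% | 17% |
| 12 | 25% | 20 | 17% | 8% |
| 18 | 17% | 13 | 11% | 6% |
| 24 | 12.5% | 10 | 8% | 4% |
| 36 | 8% | 7 | 6% | 3% |

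Visits up to month 3 that fall after release: none, because the rule waits for all participants. If release waits for the last month-6 visit, every entry in the table becomes zero and N is unchanged.

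**Dual role: side by side.** Randomization and quality control of data belong to one named role. Elimination of data for quality is foreseen. No section says who decides an elimination or that the decision is blind. Arm-aware decisions are therefore possible under the text, though not described in it.

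The 20% allowance does not size this. The plan's own step is 13 × 1.2 = 15.6, rounded up to 16 per subgroup. An increase of 20% offsets 1 − 1/1.2 = 16.7% attrition from all causes (loss to follow-up, drop-out and eliminated data), and no share is given for elimination.

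A hypothetical case shows why it still matters. Dropping one patient who lies 2 SD from the mean of a 16-patient subgroup moves that mean by 2 × SD/15. With the planning SDs of 1.9 and 2.3 (average 2.1) the shift is 4.2/15 = 0.28 MMSE points. With the largest pre-treatment MMSE spread in Table 2, read as an SD of 8.54, it is 17.08/15 = 1.14. The planned difference is 2.4. This illustrates sensitivity and is not an estimate of bias.

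**The case against.** The case on the other side is substantial, and most of it limits the point.

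- **A reader might infer that the primary result is rated unblinded.** The documents do not support that. Release waits until every participant has passed the 3-month endpoint, so all primary MMSE ratings are already made.
- **A reader might infer that release at month 3 is fixed.** The first rule sets an earliest time, not a trigger, and the second sentence may mean the end of all follow-up. Early release is one reading. Even so, if the second sentence means month 6, the subsection holds two different release points, and the text needs settling either way.
- **A reader might infer that assessors or patients receive the code.** No section says so. Unblinding is described as a step by quality control staff and the project leader before analysis. It is equally true that nothing says assessors stay masked after release.
- **A reader might infer that exclusions are made by people who know the arm.** The article does not say who makes them. The mention of eliminated data is a reason for enlarging the sample, not a procedure. Random selection, outside retesting and wider review are real safeguards, but retesting covers only sampled data and none of the reviewers is said to be masked.
- **A reader might infer an open trial from Results in Progress**, which at one point calls the study not blinded. The same section says that grouping has not been unblinded and that the authors could not tell the subgroups, so this looks like a slip. The wording should be reconciled.

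Details of data lock and exclusion review may sit in a fuller document. What stands is what the article itself fixes: a release rule that can precede the last visits, an undefined endpoint, and one role with both duties.

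**Conclusion.** The point holds in a limited form.

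**Timing.** The text permits release before follow-up is complete. On the 3-month reading, month 4 to 6 ratings of patients from about the last 3 months of accrual could be made after release: 25% of patients and 17% of those visits for 12 months of accrual, 12.5% and 8% for 24 months. This rests on uniform accrual and an assumed duration, and it becomes bias only if the code reaches raters or patients.

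**Dual role.** This is the stronger half, because it can touch primary endpoint data. Its effect cannot be sized from the article. The supported statement is that data-quality decisions can be made knowing the arm, not that they are.

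Both are worth correcting because the remedy is cheap.

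**What to change.** 1. In Stratified Randomized Groups, replace both release statements with one: the allocation is released after the last patient's 6-month assessment and data lock.
2. If a 3-month analysis is run earlier, state that assessors and patients stay masked until their 6-month visits are complete.
3. Have an existing team member with no part in data quality control or outcome assessment generate and hold the list and inform the treating physicians.
4. State who decides exclusions, and require them to be decided and signed off blind before release.
5. Reconcile the two statements on blinding in Results in Progress.

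The cost is unblinding up to about 3 months later (month 6 minus month 3) and a reassignment of duties. Sample size, treatment and visits do not change. With 18 of 80 patients included when the article was written, 62 were still to be enrolled, so the change would protect most of the data.
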